**Figure 1 figure1:**
[figure not shown]
Participant flow through the trial.

### Study Sample and Procedure

A total of 800 fathers-to-be or new fathers from within Australia will be recruited. Participants will be recruited through the SMS4dads website [36], which houses a brief introductory video explaining the SMS4dads program and information and enrolment pages. Fathers will be made aware of the Web page and the project through social media, through flyers distributed by health staff in contact with parents, and through mainstream media outlets. Interested fathers are provided with email and phone contact to enable further questions about the study to be answered.

### Inclusion Criteria

Participants will be included in the trial if they indicate having a partner who is more than 16 weeks pregnant or their infant is less than 12 weeks of age, have a mobile phone capable of receiving text messages, and they can read and understand English. There is no cost involved in receiving the text messages but access to the internet is required to respond to the Mood Tracker texts and to access the links provided to websites in the messages.

### Screening and Baseline

Expecting and new fathers will register for participation through the project website where an information statement and other materials about the project are readily available [39]. Fathers wishing to enrol can click on the “Join Up” tab located on the front page of the SMS4dads website, which will take them to the registration pages. The first registration pages assess eligibility and information for messaging purposes including their infant’s expected or actual date of birth, full name, email address, and phone number. For demographic purposes, they will be asked for their age, postal address, Indigenous status, and a question about their socioeconomic position [37]. When completing consent questions fathers will be asked to confirm that they have read the information statement and that they have no further questions about the project. They will also be asked if they would like to be informed of study outcomes, if they would be willing to participate in phone interviews about their experience of participation, and whether they would be prepared to pass an information package onto their partner. When fathers have answered these questions they will be asked to respond to four questionnaires (53 items) detailed in the following section on study measures. All questions mandate a response but fathers can report that they have no email address and that they do not wish to supply data about their socioeconomic position.

### Follow-Up Assessments

Fathers are also asked to repeat the questionnaires 24 weeks after receiving their first message.

### Randomization

Randomization was performed using a custom-built Web-based module attached to the online data collection forms. The actual randomization process was based on a random number generator with a random seed, and using random permuted blocks of 4 or 6. Allocation was 1:1 in the intervention or control arm as new users registered on the site. The Web modules were built using C#.Net (with a Visual studio integrated development environment) and a Microsoft SQL Server backend to store the generated random numbers.

From an architectural perspective, proper separation of code design principles was followed as the complete randomization feature was implemented as a contained application programming interface (API) module. The API module was only accessible from a software Application with the required granted permissions, through calls within the requesting Applications business and data access layer. This also allowed the module to be maintained without effecting the source Web application consuming its resources

### Sample Size

Sample size was based on the primary outcome of Depression Anxiety Stress Scales (DASS-21) [40] values in the intervention and control arms at 24 weeks, adjusting for baseline values. We assume an effect size of 0.5 SD Units (Cohen’s *d*) among those “distressed” fathers who report Moderate, Severe or Extremely Severe scores on the total DASS-21 (≥ 23). Aiming for power of 80%, significance level of 5%, 1:1 ratio of allocation to control and intervention, we estimate a sample size of 64 “distressed” fathers will be required in each arm of the trial. Assuming 20% of the sample recruited will be distressed (based on feasibility study data) we will require 320 fathers in each arm giving a total sample of 640 fathers. Allowing 20% for attrition and loss to follow-up, 800 fathers in total will be required to be recruited.

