### Hypotheses

It is predicted that fathers receiving the SMS4dads program will show lower levels of depression, anxiety, and distress at 24 weeks postbaseline than fathers receiving the SMS4health program. In addition, fathers’ coparenting and parenting self-confidence are predicted to be greater and use of alcohol to be less among those receiving SMS4dads than among those receiving SMS4health.

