### Data Analyses

Given that there are multiple measures of the primary outcome, ie, DASS-21 scores at baseline and 24 weeks, we will use a linear mixed–model to analyse the results. This model will handle repeated measures as well as missing data; the model will include terms for group, time, and group x time interaction, which will allow us to see if the effect is more marked in one group versus another at particular time points. Secondary outcomes such as parenting, coparenting, and alcohol scales will be analysed using similar models.

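### The 80% power and the 800-father total apply to a comparison of distressed fathers only; the all-father analysis that the article describes has no stated power

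*Protocol article*

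**What the plan says.** The Sample Size section of the protocol article takes as primary outcome the DASS-21 "values in the intervention and control arms at 24 weeks, adjusting for baseline values". The effect assumption is "We assume an effect size of 0.5 SD Units", and it is confined to "fathers who report Moderate, Severe or Extremely Severe scores on the total DASS-21", with a cut-off of 23 or more. The design parameters are "Aiming for power of 80%, significance level of 5%, 1:1 ratio of allocation to control and intervention", which give 64 distressed fathers per arm. The step to the full trial is "Assuming 20% of the sample recruited will be distressed (based on feasibility study data) we will require 320 fathers in each arm". That makes 640 fathers, raised to 800 for 20% attrition.

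The rest of the article is not limited to distressed fathers:

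- The aim, at the end of the Introduction, concerns symptoms in new fathers generally.
- Hypotheses: "It is predicted that fathers receiving the SMS4dads program will show lower levels of depression, anxiety, and distress at 24 weeks postbaseline", compared with fathers receiving the control program.
- Inclusion Criteria set no distress threshold.
- Data Analyses describes one linear mixed model for the primary outcome: "the model will include terms for group, time, and group x time interaction". It mentions no restriction to distressed fathers, no stratum and no interaction with baseline distress.

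**The concern.** A power statement belongs to one comparison in one population. Here it belongs to about 128 distressed fathers, while the hypothesis and the model concern about 640 completers, of whom some 80% are expected not to be distressed. No effect size is offered for those other fathers or for the sample as a whole.

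Two misreadings are at stake:

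- A null all-father result could be taken as coming from a test with 80% power, although nobody has shown that it has that power.
- If the benefit is concentrated among distressed fathers, the only group for which the article assumes one, the all-father test may miss it. A later distressed-only result could then be challenged because Data Analyses does not name it.

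The time at which distress is classified is also left implicit. The reference to a share of the recruited sample points to baseline, but the section does not say so. Selecting on a score taken after randomization would break the randomized comparison.

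**Working it through.** **Inputs from the Sample Size section:** d = 0.5 in distressed fathers; power 80%; significance level 5% (sidedness not stated); 1:1 allocation; 20% distressed; 20% attrition.

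**Inputs not in the article, so assumed and varied:** the effect e in non-distressed fathers, the ratio of the all-father SD to the distressed-subgroup SD, and the baseline to 24-week correlation ρ.

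**1. The plan's own figure.**

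- A two-sided 5% two-sample t-test at d = 0.5 has 79.5% power with 63 per arm and 80.1% with 64 per arm, so 64 reproduces. A one-sided test would need 50 (normal approximation), which does not match.
- 64 / 0.20 = 320 per arm; 2 × 320 = 640; 640 / (1 − 0.20) = 800.
- The chain is correct for the distressed subgroup. It takes no credit for baseline adjustment, although the section mentions it.

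**2. What the all-father comparison can detect.** With n = 320 completers per arm:

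- Unadjusted: (1.960 + 0.842) × √(2/320) = 2.802 × 0.0791 = 0.22 SD.
- Baseline-adjusted, multiplying by √(1 − ρ²): 0.2215 × 0.866 = 0.19 SD at ρ = 0.5; 0.2215 × 0.8 = 0.18 SD at ρ = 0.6.

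This step needs no assumption about who benefits.

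**3. Power under scenarios for the other fathers.** The average effect is 0.2 × 0.5 + 0.8 × e. Power is Φ(average / √(2/320) − 1.960), with equal SDs and no baseline gain.

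| e, effect in non-distressed (SD) | Average effect (SD) | Power |
|---|---|---|
| 0 | 0.10 | 24.4% |
| 0.05 | 0.14 | 42.5% |
| 0.10 | 0.18 | 62.4% |
| 0.15 | 0.22 | 79.5% |
| 0.20 | 0.26 | 90.8% |
| 0.50 | 0.50 | over 99.9% |

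First row in full: 0.10 / 0.0791 = 1.265; 1.265 − 1.960 = −0.695; Φ(−0.695) = 0.244.

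**4. Sensitivity of the e = 0 row.**

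- Baseline adjustment, average effect 0.10 / √(1 − ρ²): 30.9% at ρ = 0.5, 35.2% at ρ = 0.6, 42.5% at ρ = 0.7.
- Group-by-time term read as a difference in change, SD √(2(1 − ρ)): 24.4% at ρ = 0.5, 37.2% at ρ = 0.7.
- All-father SD relative to subgroup SD, unadjusted: 71.6% at a ratio of 0.5 and 13.2% at 1.5.

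**5. Effect in the others that restores 80% power with adjustment.** (0.192 − 0.10) / 0.8 = 0.115 SD at ρ = 0.5; (0.177 − 0.10) / 0.8 = 0.10 SD at ρ = 0.6.

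**The case against.** The strongest reply is that the article assumes nothing about non-distressed fathers, so no low power figure follows from it. That is right. A reader might infer that the plan's own assumptions give about 24% power, or that a null result is the likely outcome even if those assumptions hold. The article supports neither inference. The 24% needs three additions: zero effect in the other 80%, equal SDs, and no gain from baseline. The messages are written for new fathers in general, so zero benefit in the others is not a premise of the article. With baseline adjustment, an effect of about 0.10 to 0.12 SD in them would bring the all-father power back to 80%.

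A second reply is that this is a condensed article and that a subgroup analysis may sit in an analysis plan not shown. This also stands in part: the text does not show that no distressed-only analysis exists. It does not remove the mismatch, because the article itself fixes both a sizing population and a model, and the two differ.

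A third reply is that publishing the cut-off, effect size and target number before follow-up ends protects a later distressed-only result from the charge of being post hoc. That helps, but a threshold in a sample size paragraph is weaker protection than a named analysis with the time of classification stated.

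Finally, making the distressed subgroup primary would change the question posed in the aim and hypotheses. That is a design decision for the sponsor and does not follow from this point.

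**Conclusion.** The point holds as a mismatch between the stated power and the stated analysis. The 80% power, and the 800 fathers derived from it, refer to 64 distressed fathers per arm at d = 0.5. The all-father analysis has no stated power.

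The firmest measure of size is the detectable all-father difference: about 0.22 SD unadjusted with 320 completers per arm, or 0.18 to 0.19 SD if the baseline correlation is 0.5 to 0.6. Those correlations are assumptions, since the article gives none.

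The power figures are scenarios only. With equal SDs, unadjusted power runs from about 24% if the other fathers gain nothing (31 to 35% with baseline adjustment at those correlations), through about 80% if they gain 0.15 SD, to over 99.9% if everyone gains 0.5 SD. The article gives no basis for choosing among these, so the 80% cannot be carried over to the all-father test. Nor can that test be called underpowered outright.

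**What to change.** Before 24-week data are compared by arm:

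- In Sample Size, state that the 80% power refers to the comparison within distressed fathers. For the all-father analysis, replace the 80% claim with its own detectable difference: about 0.22 SD unadjusted with 640 completers, plus a baseline-adjusted value if a correlation can be justified.
- In Data Analyses, add a prespecified comparison in fathers whose baseline DASS-21 total is 23 or more, and a group-by-baseline-distress term to describe effect modification.

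If the sponsor in fact intends the distressed subgroup as the primary population, it should say so, define the subgroup at baseline, place the all-father comparison second in a fixed sequence, and align the aim and hypotheses.

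The first route costs wording only: no more fathers and no new data, because every father completes the DASS-21 at enrolment. The alternative also needs no new data, but it changes the trial's primary question while follow-up is under way, so it should be dated and justified.

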### Program Content, Tone, and Design

The program content includes an established corpus of relationship-focused messages developed for a related feasibility study using an iterative consultation process with parents, academics, and practitioners (N=46) [41,42]. Messages aim to provide new fathers with information, support them in caring for their own physical and mental health, nurturing strong relationships with their child, and developing strong parenting partnerships with their partner. Messages are timed according the babies expected or actual date of birth and thereby designed to address issues that are likely to be occurring for the father when the information arrives. Messages, including links, are limited to 160 characters and designed to engage with fathers through humor, by use of the baby’s voice, and through an encouraging, nonjudgemental tone. Approximately one third of messages (n=98) contain links to online sources of information directly related to the message content [41].

A father participating in the full 77-week program will receive 294 messages. These are usually delivered on a 4-week cycle (5 messages in week 1, 4 in week 2, 3 in week 3, and 3 in week 4) totalling 15 messages. Some messages address particular issues such as alcohol consumption (n=25) and others link to the Mood Tracker application (n=30). Mood Tracker messages ask fathers to respond to questions about their mood on a 5-point scale. Fathers indicating high levels of distress on Mood Tracker will be automatically linked to appropriate websites and offered the opportunity to be contacted by a phone counselling service experienced in paternal perinatal support.

### Study Measures

Measures will be constrained to minimise the burden on participants. Questionnaires employed in the study include the DASS-21 (21 items) [38], the Alcohol Use Disorders Identification Test (AUDIT-C) (3 items) [40], the Short Version Coparenting Relationships Scale (CRS) (14 items) [43], and the Karitane Parenting Confidence Scale (KPCS) (15 items) [44].

The DASS-21 is a truncated version of a 42-item measure designed to assess three distinct, but empirically related, states of mental health. The validity of the three scales (depression, anxiety, and stress) that make up the DASS-21 has been demonstrated through strong correlations with established measures of each factor in diverse populations. The reliability of the subscales has been established in a large normative sample (N=717) with correlations between subscales and relevant measures reported for depression (0.81), anxiety (0.73), and stress (0.81) [39].

The AUDIT-C is a 3-item measure of alcohol consumption. The AUDIT-C was found to be more reliable than telephone interview in detecting heavy drinking in a sample (N=243) of known drinkers [45].

The CRS short version is a truncated version of the 35-item multi-domain questionnaire designed to assess parent perceptions of the strength of their parenting relationship with their partner. The validity of the CRS has been determined against established scales of coparenting quality and the total scale reliability (Cronbach's alpha) across three waves of measurements ranging from 0.81 to 0.85 [43].

The KPCS is designed to assess maternal and paternal perceptions of parenting self-efficacy (PSE) in the Australian context. The validity of the KPCS has been demonstrated against established measures of PSE and the authors report a total scale reliability (Cronbach's alpha) of 0.81 in a normative sample (N=27) [44].

### Data Analyses

Given that there are multiple measures of the primary outcome, ie, DASS-21 scores at baseline and 24 weeks, we will use a linear mixed–model to analyse the results. This model will handle repeated measures as well as missing data; the model will include terms for group, time, and group x time interaction, which will allow us to see if the effect is more marked in one group versus another at particular time points. Secondary outcomes such as parenting, coparenting, and alcohol scales will be analysed using similar models.

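### The mixed model as specified does not give the baseline-adjusted 24-week DASS-21 comparison on which the trial was sized; the cost is some precision, not bias

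*Protocol article*

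**What the plan says.** Two sections of the protocol article describe the primary comparison.

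- **Sample Size** sets the target as DASS-21 "values in the intervention and control arms at 24 weeks, adjusting for baseline values". The calculation starts from this effect: "We assume an effect size of 0.5 SD Units (Cohen’s *d*) among those “distressed” fathers". With 80% power, a 5% test and equal arms, the section reaches its core number: "we estimate a sample size of 64 “distressed” fathers will be required in each arm of the trial". The totals then follow in two steps. The first scales up by the expected share of distressed fathers, to 320 per arm and 640 overall. The second adds a loss allowance: "Allowing 20% for attrition and loss to follow-up, 800 fathers in total will be required to be recruited".
- **Data Analyses** treats the DASS-21 at baseline and at 24 weeks as repeated outcomes in a linear mixed model, chosen partly to handle missing data, and states that "the model will include terms for group, time, and group x time interaction". The interaction is the only term given a purpose: to show whether one group has the larger effect at given times. The section mentions no baseline covariate and no constraint that the arms share a baseline mean. Secondary scales are to be analysed with similar models.

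The **Hypotheses** section predicts "lower levels of depression, anxiety, and distress at 24 weeks postbaseline" for SMS4dads. It fixes the time point but is silent on adjustment, so the promise of baseline adjustment rests on the Sample Size section alone.

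**The concern.** There are only two measurement times, and the first precedes treatment. A model with free group, time and interaction terms fits four separate means, so it allows the arms to differ at baseline, although randomisation makes the true baseline means equal. Its treatment contrasts therefore do not use the baseline score as an adjustment would:

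- the interaction is the difference between arms in mean change;
- the group contrast at 24 weeks is, in complete data, the plain difference in 24-week means.

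A reader of Sample Size expects a third quantity, the 24-week difference at equal baseline score. That quantity is never less precise than the other two and is not pulled about by chance baseline imbalance. At stake are some avoidable loss of precision and a primary contrast that two sections describe differently.

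**Working it through.** **1. The plan's own figure.** Inputs from Sample Size: d = 0.5, 80% power, 5% significance, 1:1 allocation. A two-sided, unadjusted two-sample t-test needs 63.8, so 64 per arm, with 80.1% power. Then 64/0.20 = 320 per arm, 640 in total, and 640/0.80 = 800. All the figures reproduce. No credit is taken for baseline adjustment.

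**2. What the interaction estimates.** In simulated complete data (64 per arm, ρ = 0.5), the group x time coefficient and the difference in mean change were both −0.6274. Standard errors were 0.171 for the interaction, 0.139 for ANCOVA and 0.143 for a mixed model with a common baseline mean.

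**3. All fathers, equal SDs.** Set the SD to 1 at both times. The article does not give ρ, so it is an assumption.

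- Complete cases: Var(change) = 2(1−ρ) and Var(adjusted) = 1−ρ², so the ratio is 2/(1+ρ).
- With 20% random loss, for every 80 randomised per arm 64 are followed. The likelihood-based interaction has variance proportional to (1−ρ²)/64 + (1−ρ)²/80, and the adjusted contrast to (1−ρ²)/64. The ratio is 1 + 0.8(1−ρ)/(1+ρ).

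| ρ | Ratio, complete cases | Ratio, 20% loss |
|---|---|---|
| 0.3 | 1.54 | 1.43 |
| 0.4 | 1.43 | 1.34 |
| 0.5 | 1.33 | 1.27 |
| 0.6 | 1.25 | 1.20 |
| 0.7 | 1.18 | 1.14 |

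Simulation with 20% loss gave standard errors of 0.204 versus 0.169 (ρ = 0.3), 0.173 versus 0.155 (0.5) and 0.134 versus 0.125 (0.7), in line with the last column. Both estimators averaged close to the true −0.5, so neither is biased.

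**4. The distressed subgroup that is powered.** These fathers are selected on a high baseline score, so their baseline variance is restricted. Model them as the top 20% of a normal baseline:

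- cut-point 0.8416; mean of the selected group 0.2800/0.20 = 1.3998;
- baseline variance k = 1 + 0.8416 × 1.3998 − 1.3998² = 0.219;
- Var(adjusted) = 1−ρ²; Var(change) = 1−ρ² + k(1−ρ)²; Var(24 weeks) = 1−ρ² + kρ²;
- effect = 0.5 × SD at 24 weeks within the subgroup.

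At ρ = 0.4 the variances are 0.840, 0.919 and 0.875, and the effect is 0.5 × √0.875 = 0.468. With 64 per arm the standard errors are √(2 × 0.919/64) = 0.169 for change and √(2 × 0.840/64) = 0.162 for the adjusted contrast. Power from the t distribution:

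| ρ (all fathers) | Interaction | Baseline-adjusted |
|---|---|---|
| 0.3 | 76.5% | 81.0% |
| 0.4 | 78.2% | 81.7% |
| 0.5 | 80.1% | 82.8% |
| 0.6 | 82.5% | 84.5% |
| 0.7 | 85.8% | 87.0% |

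The unadjusted 24-week comparison stays at 80.1% by construction. The interaction falls below it only when ρ is under 0.5.

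**The case against.** The strongest reply is that an article need not name the primary contrast or the handling of baseline means; an analysis plan may do so. In part this stands. The article never says in so many words that the interaction is the primary test, and a reader who infers that a change-score test is firmly planned goes further than the text. But the model terms are listed and the interaction is singled out, and neither of the model's natural contrasts matches Sample Size. The mismatch is therefore in what is stated, not in what is left out.

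Three other stronger readings are tempting and not supported.

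- **A large power loss.** With 64 per arm and equal SDs at both times, power at ρ = 0.4 would be about 73% for change against 86% for the adjusted contrast. Equal SDs are implausible in fathers selected on a high baseline score. Allowing for selection leaves a gap of 2 to 4 points between ρ = 0.4 and 0.6. The complete-case ratios also overstate the loss, because the mixed model keeps fathers with baseline data only.
- **An error in the sample size.** The figures reproduce. An unadjusted calculation is conservative for a baseline-adjusted analysis.
- **A contradiction with Hypotheses.** That section says nothing on adjustment.

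**Conclusion.** The point holds as an inconsistency with a modest efficiency cost; its importance is minor to moderate. Sample Size promises a baseline-adjusted 24-week comparison, and the model in Data Analyses does not produce one. A reader might infer bias or an invalid test, but under randomisation both contrasts are unbiased.

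The size depends on a correlation that the article does not give and on which fathers are analysed. For ρ between 0.4 and 0.6, the interaction has 20% to 34% more variance than the adjusted contrast across all fathers, assuming equal SDs and 20% random loss. In the distressed subgroup the difference is about 3.5 power points at ρ = 0.4 and 2 points at ρ = 0.6, assuming a normal baseline cut at its top fifth. Neither result shows that the planned 80% is missed; in the subgroup a shortfall arises only if ρ is below 0.5, and at ρ = 0.4 it is about 2 points.

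**What to change.** - **Data Analyses:** keep the linear mixed model but constrain baseline means to be equal across arms, with terms for time and group x 24 weeks and no free group main effect. Let the variances at the two times differ. This keeps fathers who have only a baseline score in the model. Name the resulting baseline-adjusted 24-week difference in DASS-21 as the primary contrast. ANCOVA of the 24-week score on group and baseline among completers is a close alternative, but not an identical one.
- **Secondary scales:** use the same form wherever a baseline measure exists.
- **Sample Size:** state that 64 per arm is the unadjusted two-sample t-test figure and that baseline adjustment is a margin on top of it.

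The cost is a few lines of wording, settled before the 24-week data are analysed. No extra data, visits or software are needed.
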